## 4.6 Schedule

**Table 1:** Schedule of the SUPPORT study with indication of the individual work packages and milestones

| Work package no. | Milestone (▼)                                                                                              | Year 1
08/15 – 07/16 | Year 2
08/16 - 07/17 | Year 3
08/17 – 07/18 |
|------------------|------------------------------------------------------------------------------------------------------------|-------------------------|-------------------------|-------------------------|
| 1                | Study preparations (preparation of study documents, recruitment and randomization of hospitals) completed. | ▼                       |                         |                         |
| 2                | First patient enrolled                                                                                     |                         | ▼                       |                         |
|                  | 50% of the total 500 patients included                                                                     |                         | ▼                       |                         |
|                  | Follow-up completed, database closed                                                                       |                         |                         | ▼                       |
| 3                | Statistical analysis completed                                                                             |                         |                         | ▼                       |
|                  | Final report and scientific manuscript prepared                                                            |                         |                         | ▼                       |

**Table 2:** Description of the individual milestones of the SUPPORT study.

| No. | Milestone                                     | Time after project start (months) |
|-----|-----------------------------------------------|-----------------------------------|
| ▼1  | Preparation and establishment of the study.   | 6                                 |
| ▼2  | Inclusion of 1st patient.                     | 10                                |
| ▼3  | Inclusion of the 250th patient.               | 18                                |
| ▼4  | Inclusion of the last patient.                | 30                                |
| ▼5  | End of follow-up and closure of the database. | 33                                |
| ▼6  | Submission of the scientific manuscript.      | 36                                |

The SUPPORT study timeline is shown in **Table 1** and the individual milestones are shown in **Table 2**. The expected total study duration is 36 months. No interim evaluation is planned. Enrollment in the study will end with the 500th enrolled patient. The study duration per patient is 90 days. The study ends 90 days after inclusion of the 500th patient. The study is divided into different work packages:

#### Work package 1: Study preparation

After preparation of the study documents (study protocol, patient information and informed consent) and obtaining the ethics votes, the study folders (TMF, ISF), the Case Report Form (CRF), the study database as well as the recruitment and randomization of the participating hospitals are prepared. In addition, the IT infrastructure for data transfer is set up.

#### Work package 2: Study implementation

In this project phase, patient inclusion in the participating clinics, telephone consultation with the treating physicians in the clinics, as well as documentation of the data in the CRF and data checking (query management) and follow-up surveys (calls to the patients/primary care physicians) will take place. The study completion of the last patient is planned in month 30.

#### Work package 3: Study completion

The statistical evaluation and interpretation of the data, the preparation of the final report, the publication of the results in professional journals and their presentation at (scientific) professional events are carried out.

## 5 Participating study centers

This study will include at least 15 of the up to 39 hospitals participating in AlertsNet 2.0 and a total number of 500 patients. Participating hospitals will be randomized into 2 groups with 2 sequences: A-B or B-A. Here, A represents the intervention and B the control group ("standard of care"). During the intervention, treating physicians at participating hospitals will receive unsolicited telephone consults recommending an evidence-based set of interventions to treat SAB (11).

The condition for participation here is that the laboratory to which a hospital sends its microbiological samples is connected to AlertsNet2.0. With regard to the IT concept, reference is made to the AlertsNet2.0 application.

Qualification of the participating centers or treating physicians beyond routine clinical work is not necessary. The telephone consultation is carried out by a clinical infectiologist or a physician with sufficient infectiological experience. There is no minimum number of patients to be included. The change of the groups takes place individually for each center after inclusion of the first 17 patients or after 12 months at the latest.

## 5.1 Test center directory

Participating study sites are identified in **Section 14.1**.

## 5.2 Conditions for participation in the study

A condition for a hospital's participation in the study is the hospital's connection to the AlertsNet platform, which allows the information about the presence of an *S. aureus-positive* blood culture to be sent directly to the SUPPORT study center. There are no restrictions regarding the size of the hospital or the patients treated. The responsibilities of the study centers are specified in cooperation agreements.

Patients participating in the study must meet the inclusion criteria stated in **Section 6.1**. No exclusion criterion must be present (see **Section 6.2**).

## 6 Patient selection

### 6.1 Inclusion criteria

All adult (at least 18 years old) patients, regardless of gender, with diagnosed SAB (positive blood culture) who have given their written consent to participate in the study should be included. Re-enrollment of a patient who had already been included in the study will only occur if the 2nd SAB episode occurs more than 90 days after the 1st SAB episode and there is no evidence of recurrence due to deep-seated infection. In this case, the patient will be re-educated and must again consent to study participation. In principle, he will be managed as a new patient. It must be noted in the patient file and in the CRF that this is a 2nd SAB episode.

### 6.2 Exclusion criteria

Patients will not be included in the study if any of the following criteria are present:

- Positive blood cultures with only other pathogens in the blood culture (patients in whom more than one bacterial species is detected are included if one pathogen is *S. aureus*).
- S. aureus* infections without bacteremia (e.g., superficial wound infections with evidence of *S. aureus*).
- Patients receiving palliative care, with treatment limitations or cessation (e.g., DNR order), or with life expectancy < 90 days due to underlying disease.

## 7 Course of studies

### 7.1 Detailed study process

Information about a microbiological blood culture result *positive* for *S. aureus* is automatically reported to the SUPPORT team via the AlertsNet infrastructure (Electronic Blood Culture Registry, EBCR). However, data management is done separately. The system sends a fax to the treating hospital with the patient's clinical name, -year of birth, *subject identification code* (SIC) and microbiological findings. The study center at the UKJ, which is informed at the same time, does not receive any clear name information but only the information of a SAB detection in a specific institution and the automatically generated case code (SIC). The study center contacts the study physician at the clinical institution and, based on the relevant positive microbiological findings and using the SIC, asks for the patient to be included in the study. If the patient agrees to participate in the study after being informed by the study physician, the signed consent form is faxed to the study center. Only with this fax does the study center thus receive clear name information on the SAB-positive patient. Thereupon, for patients of the intervention arm, the telephone consultation with the treating physician is performed and subsequently the consultation is confirmed by fax (incl. therapy proposal). For patients in the control group (no infectious disease consultation), the two aforementioned steps are omitted. After inclusion in the study, only the informed consent form is faxed to the study center. A consultation is not performed for these patients.

The SUPPORT study nurse documents the data of the study patients pseudonymously in the CRF as soon as possible during her on-site visits. After 30 and after 90 days, a follow-up call is made to the patients by the study center. The contact details for this are recorded separately in the consent form (**Figure** and **Section 14.2**).

[figure not shown]

\*EBCR: Electronic Blood Culture Registry

325

326 **Figure:** Flow chart for the SUPPORT study.

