| Target population/disease             | Patients with Staphylococcus aureus bacteremia.                                                                                                                                                                                                                                                                                                                                                                                                                                                                                                                                                                                                                                                |
| Study design/methodology              | Prospective randomized, single-blind, controlled two-arm (intervention vs. control) multicenter trial with cross-over design. The intervention is the provision of a non-requested infectious disease telephone consult. The control group will not receive a telephone consult. The study duration in one group before cross-over is to be 12 months.
Randomization: 1:1 cross-over
Blinding: simple, i.e., patients are not told which group (intervention or control) they are in; blinding of treating physicians/study centers is not possible.
Intervention group: non-requested telephone consult.
Control group: no telephone consultation, follow-up only.
Follow-up: 90 days |
| Aims of the clinical trial/objectives | Primary Objective:
To demonstrate efficacy (30-day all-cause mortality) and safety of nonrequested infectious disease consults compared with standard care without telephone consults in patients with SAB.                                                                                                                                                                                                                                                                                                                                                                                                                                                                                 |

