## 327 Checking the inclusion and exclusion criteria

328 The examination of the inclusion and exclusion criteria of potential study patients  
329 ("screening") is performed using a predefined checklist. All patients who meet the inclusion  
330 criteria are documented in a central "Screening Log" (**Appendix 2**) at the study center. This  
331 log will also indicate whether the patient was included in the study or for what reason, if any,  
332 the patient was not included. If a patient fulfills all inclusion criteria and there are no exclusion  
333 criteria, he/she is to be entered in the patient identification list with the date of study  
334 inclusion.

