## 385 7.7 Follow-up surveys

386 The survival of the patients and the recurrence rate will be recorded up to 90 days after  
387 diagnosis of SAB. For this purpose, the patients or, if they are not available, the primary care  
388 physician or the study centers will be interviewed by telephone 30 and 90 days after  
389 diagnosis. Patient visits are not planned.

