## 9 Biometrics

### 9.1 Endpoints

The primary endpoint of the study is 30-day all-cause mortality of patients starting from the time of SAB diagnosis.

The secondary endpoints are:

- Fulfillment of 6 of the defined quality indicators (yes/no).
- 90-day all-cause mortality starting from the time of SAB diagnosis.
- 90-day recurrence rate starting from the time of SAB diagnosis.
- Progression of SAB to sepsis/septic shock within the 90-day period (based on time of SAB diagnosis) (yes/no).
- Presence/development of septic metastases (abscesses, spondylodiscitis, osteomyelitis, endocarditis, etc.) within the 90 days (based on the date of SAB diagnosis) (yes/no).

Other parameters recorded:

Patient demographic parameters, Charlson comorbidity index (23). Infection focus, SIRS severity on admission/diagnosis, sensitivity to methicillin, antibiotic therapy performed, Pitt bacteremia score (24), cause of infection, primary site of *S. aureus* infection.

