The microbiology laboratory that examines the blood cultures sent in creates a laboratory report for each blood culture and sends it back to the clinic concerned. The findings are also recorded in the AlertsNet EBCR. After this, a semi-automated data exchange begins, which in the case of clinically relevant positive findings provides for the request for documentation of clinical data on the patient concerned by fax to the clinical facility (see AlertsNet technical IT concept version 4.3). If *S. aureus* is detected, in addition to informing the sending hospital, a fax message is automatically generated for the SUPPORT study center. For data protection reasons, this fax only contains pseudonymized data - personal data are only transmitted from the study centers to the SUPPORT study center after the patient has given his/her consent. A patient pseudonym is automatically generated for each finding/database entry (SIC; see **Section 10.1**). In addition to the SIC and the time of reporting, the clinical study center receives the clear names by fax; the SUPPORT study center in Jena receives only the SIC by fax. Only when the SAB-positive patient has consented to study participation does the SUPPORT study center receive his or her name and contact details for the planned telephone follow-up interview with a fax copy of the consent form (see study procedure in Section 7.1).

The transmission of personal data takes place exclusively via https, VPN connections or by fax.

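### 90-day recurrence has no definition and is taken from telephone calls by the unblinded study center, on forms with no recurrence item, while hospital culture records go unused for it

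*Protocol*

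**What the plan says.** - **Endpoint.** Section 9.1 lists the "90-day recurrence rate starting from the time of SAB diagnosis". The synopsis and section 3.2 list it too. None of the three says what counts as a recurrence.
- **Source.** Section 7.7: "The survival of the patients and the recurrence rate will be recorded up to 90 days after" diagnosis. The means is a call to the patient. If the patient is not available, the primary care "physician or the study centers will be interviewed by telephone 30 and 90 days after" diagnosis. Section 7.8 plans no patient visits.
- **Caller.** Section 7.1: "After 30 and after 90 days, a follow-up call is made to the patients by the study center".
- **Role of the caller's center.** Section 7.1 has the consent form faxed to the study center, after which, "for patients of the intervention arm, the telephone consultation with the treating physician is performed and subsequently the consultation is confirmed by fax". Section 4.6 puts consults and follow-up calls in the same work package.
- **Blinding.** Only patients are blinded. The synopsis says that "blinding of treating physicians/study centers is not possible". No blinded caller or assessor is named.
- **Forms.** Sections 10.3.2.17 and 10.3.2.18 have four items each: contact achieved, recent hospitalization with reason, death, and new complaints.
- **Laboratory reports.** Under section 10.4, when *S. aureus* is detected, "a fax message is automatically generated for the SUPPORT study center", in addition to the report to the hospital. These reports are described for case finding and enrollment, not for the recurrence endpoint.

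**The concern.** Section 6.1 identifies SAB by a positive blood culture. A recurrence would naturally be established the same way, yet the plan relies on what a patient, a family doctor or hospital staff say by telephone. A patient may be unable to tell recurrent bacteremia from another re-admission. Because the forms have no recurrence item, someone must infer the event from a reported reason for admission, with no stated rule.

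Two consequences follow. Missed events lower power even when they are missed equally in both arms. If the questioning or the classification differs by phase, which is possible when the calling center knows the phase, the comparison itself is biased.

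**Working it through.** The protocol gives no recurrence rate, effect size or power for this endpoint, so there is no figure to reproduce. The check is a comparison of sections, followed by an illustration on assumed rates.

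**1. Does the planned data capture yield the endpoint?** Section 9.1 needs recurrence within 90 days. Section 7.7 assigns it to the calls. The call forms contain no such item. Two chart-review items come close: further positive blood cultures (10.3.2.6) and progression of the SAB at discharge (10.3.2.15). The first has no time window, the second stops at discharge, and neither is tied to recurrence.

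**2. Is the calling center blind?** Section 7.3 keeps the randomization list inaccessible. But under section 7.1 the study center's receipt of the consent fax leads to a consult in one arm and none in the other, so the center has to know each hospital's current phase. The protocol does not say whether the individual caller knows it.

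**3. Is a better source within reach?**
- The hospital receives the laboratory report with the patient's name and code (7.1).
- It keeps a list linking code, full name and date of birth (10.1).
- The study nurse already visits and extracts data from the records (10.3.1, 11.2).
- Section 6.1 already requires a second episode to be recognized and dated against the 90-day limit before re-enrollment.

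A repeat positive culture can therefore be matched at the hospital without sending new identities to the study center.

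**4. Limits of that source.** The reports cover connected laboratories only (section 5). The addendum lets sites enroll before connection, with telephone or fax reports. The study center sees a new pseudonym for each finding (10.4), so it cannot match alone. One hospital's list will not identify a patient re-admitted elsewhere.

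**5. Illustration.** Assumptions not in the protocol: the true recurrence rates and the detection rates. From the synopsis: at least 450 patients analyzed, so 450/2 = 225 per condition. Clustering is ignored; two-sided alpha is 5%.

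Observed rate = true rate × detection rate. With p1, p2 the observed rates, p̄ their mean and n = 225,

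probability = Φ{ [ |p1 − p2|√n − 1.96√(2p̄(1 − p̄)) ] / √(p1(1 − p1) + p2(1 − p2)) }.

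Worked case: true rate 10% in both arms, detection 90% (control) and 70% (intervention). The observed rates are 0.10 × 0.90 = 9% and 0.10 × 0.70 = 7%, ratio 0.07/0.09 = 0.78. Then [0.02 × 15 − 1.96√(2 × 0.08 × 0.92)] / √(0.0819 + 0.0651) = (0.300 − 0.752)/0.383 = −1.18, and Φ(−1.18) ≈ 12%.

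Chance of a false significant benefit (nominal 2.5%):

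| True rate, both arms | 90% vs 70% detected (ratio 0.78) | 90% vs 60% detected (ratio 0.67) |
|---|---|---|
| 3% | 6% | 9% |
| 5% | 8% | 13% |
| 10% | 12% | 23% |

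The direction is equally assumed: swapping 90% and 70% gives 0.90/0.70 = 1.29.

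With equal detection in both arms and a true halving from 10% to 5%, power is about 52% at full detection, 38% at 70% detection and 34% at 60%.

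**The case against.** The strongest reply has five parts.

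- **The definition may sit elsewhere.** An analysis plan or the study manual (section 11.1) could define recurrence. That is fair for the definition alone. The data source, the caller and the form content, however, are fixed in the protocol, and they do not suit the endpoint.
- **Bias by arm is not shown.** Patients are blinded, the questions are concrete, and the family doctor or hospital is a fallback. No section says that the consulting physician makes the calls; section 5 says only that consults come from an infectious disease specialist or a physician with enough experience in the field. This stands: differential error is possible, not demonstrated. Poor capture does not depend on it.
- **The trial does not receive every later culture.** A reader might infer that it does. The limits in step 4 of the working rule that out. Nor does the protocol call recurrence a culture-defined endpoint; that is an inference from how SAB is diagnosed.
- **The screening log does not fill the gap.** Section 7.1 says the "log will also indicate whether the patient was included in the study or for what reason, if any", which might suggest that early repeat episodes appear there. But the log holds patients who meet the inclusion criteria, and the 90-day re-enrollment rule is part of those criteria. A repeat episode within 90 days need not be logged.
- **Counting any new positive culture would add its own bias.** Follow-up blood cultures are among the recommended measures (10.3.2.13). They may be taken more often after a consult, and persistent bacteremia would then be counted as recurrence more often in the intervention arm. This stands and shapes the fix.

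**Conclusion.** The point holds in this form: an undefined secondary endpoint is collected by telephone from an unblinded center, on forms that do not ask for it, while records that could confirm it are not used for it. This is worth correcting, but it does not threaten the main result. All-cause mortality is far less open to this error, and section 9.5 makes the confirmatory claim for the primary endpoint only.

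The size of any bias is unknown. The ratios and probabilities above show scale under assumed recurrence and detection rates and ignore clustering; they are not estimates for this trial. A reader might infer that recurrence will be biased in favor of the consult. The documents support neither that direction nor any particular amount.

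**What to change.** 1. In sections 7.7 and 9.1, define recurrence as a new *S. aureus*-positive blood culture within 90 days of diagnosis that a pre-stated rule, identical in both arms, separates from persistent bacteremia of the index episode. Follow-up cultures prompted by the consult must not count by themselves.
2. Add a recurrence item to the 90-day CRF.
3. Confirm it from hospital microbiology records or laboratory reports, matched through the site's identification list at the nurse's planned visits.
4. Keep the 30- and 90-day calls, and use them to flag re-admissions, including those to other hospitals, for a record check.
5. Where feasible, have events classified without sight of the phase. The nurse records group allocation in the CRF (10.3.2.1), so record matching alone does not blind the classification.

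The cost is a definition, one CRF item and some added record checking at visits already planned. Recurrences cultured at other hospitals or in unconnected laboratories will still depend on the call.
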